#### Recruitment {15}

Participants will be recruited online via social media and mailing lists, as well as through local inpatient clinics and gynecologists. Patients interested in participation will receive a link to the online screening for our trial.

### Assignment of interventions: allocation

#### Sequence generation {16a}

Participants will be randomized to either the treatment or the control group using blockwise randomization. This is to ensure balanced group size even when the target sample size cannot be reached. Block size will not be shared with researchers running the trial.

#### Concealment mechanism {16b}

A web-based randomization system will be used to implement the planned allocation sequence.

#### Implementation {16c}

Randomization will be implemented by a research assistant who is not involved in the trial in any form. Participants will be informed about their allocation via mail.

### Assignment of interventions: blinding

#### Who will be blinded {17a}

Due to the nature of the planned intervention and trial design, researchers and participants will not be blinded to the allocated trial arm.

#### Procedure for unblinding if needed {17b}

There is no need for any kind of unblinding procedure, as no one involved is blinded.

### Data collection and management

#### Plans for assessment and collection of outcomes {18a}

Data will be assessed online via self-report measures. Primary and secondary outcomes will be assessed at baseline, post-treatment, at a 3-month follow-up and, for the intervention group, at a 12-month follow-up. Control variables will be assessed at baseline only; measures for process evaluation will be assessed weekly during treatment and at post treatment as well as follow-up. For more details on outcome measures see {12}.

#### Plans to promote participant retention and complete follow-up {18b}

Participants will be contacted for follow-up via e-mail. The data are collected online, reducing as many barriers as possible (e.g., having to schedule an in-person appointment or sending the questionnaires back). There is no additional incentive for participants to complete the trial. Based on our experience working with patients who suffer from endometriosis, the sample is usually grateful for any research conducted on endometriosis and tends to be very eager to participate.

#### Data management {19}

Every participant will get an individual trial subject number used to identify them throughout the trial. Researchers involved in the trial will monitor data entry and check for any missing data or anomalies.

#### Confidentiality {27}

All data will be stored on local servers of the Philipps-University Marburg according to GDPR and local policy. All data, including collected personal information, will be kept strictly confidential.

#### Plans for collection, laboratory evaluation, and storage of biological specimens for genetic or molecular analysis in this trial/future use {33}

There are no plans for collection and evaluation of biological specimens.

### Statistical methods

#### Statistical methods for primary and secondary outcomes {20a}

Analysis will be conducted based on the intention-to-treat (ITT) principle, and two-sided *p*-values < .05 will be considered statistically significant. Results will be reported according to the Consolidated Standards of Reporting Trials (CONSORT, [53]). Baseline data will be summarized by treatment group and total. We will report categorical data as *N* (%), continuous data as mean (SD). Primary outcome analysis will be performed as a general linear model comparing the difference in mean EHP-30 + 23 score and pain scores between groups with repeated measures (baseline, post-treatment, 3-months follow-up). With this approach, all participants providing data for at least one point of measurement will be included. The Holm-Bonferroni Method [54] will be implemented to account for the testing of multiple hypotheses due to nomination of two primary outcomes. For secondary outcomes, we will use analysis of covariance models to conduct possibly necessary adjustment for baseline characteristics. If any non-foreseeable changes occur during the trial, we will adjust the statistical analysis plan accordingly. Sensitivity analyses will be performed to investigate the possible influence of missing data on the robustness of the results.

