### Trial design {8}

This is a randomized-controlled, two-armed, superiority trial testing the efficacy of an 8-week iCBT training in improving HRQoL in patients with endometriosis against a waitlist control group. Randomization will be balanced with a 1:1 ratio for patient allocation to the intervention group and waitlist control group. Identifying potential moderators and mediators of treatment outcome will also be a component of this trial.

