### Outcomes {12}

#### Primary outcome measures

The primary outcomes are improvements in endometrioses-related QoL and pain during menstruation and across the cycle, as well as pain-related disability in the time between baseline and follow-up. Greater improvements are expected in the intervention group compared to the control group. Endometriosis-related QoL will be assessed using the Endometriosis Health Profile-30 + 23 (EHP-30+23) [55], which measures endometriosis-related burden across different domains of everyday life considered relevant to patients with endometriosis. The core questionnaire of 30 items is complemented by a 23-item modular questionnaire with six subscales (work life, relationship with children, sexual intercourse, medical profession, treatment, and infertility). Items are rated on a Likert scale ranging from 0 to 4. A score ranging from 0 to 100 is calculated for the core questionnaire as well as for each modular subscale, with 0 indicating the best possible quality of life.

Pain will be measured using visual analog scales. Pain-related disability will be assessed using the Pain Disability Index (PDI) [56], a 7-item questionnaire measuring the degree of disruption in different aspects of everyday life caused by chronic pain (e.g., family/home responsibilities, recreation). Each item is rated on an 11-point Likert Scale (0–10). Raw scores for all items are added together, with higher scores indicating higher degrees of disruption caused by chronic pain. Primary outcomes will be assessed at baseline, post-treatment, and at 3 months past treatment, as well as at 12 months past treatment for the intervention group.

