#### Sample size {14}

Because this is the first published study to test the efficacy of iCBT for patients with endometriosis, there is not much data available to guide sample size calculations. We estimated an effect size of *f* = 0.25, drawing on another trial in women’s health that tested efficacy of iCBT in PMDD [42]. A total number of 120 participants are needed with significance of *p* < .05 and 95% power.

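### The primary repeated-measures analysis counts baseline as an outcome level, names no contrast or visit, and does not adjust for baseline; one pre-set, baseline-adjusted contrast would be clearer and usually more powerful

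*Protocol article*

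**What the plan says.** Section {20a} describes the primary analysis as a general linear model "comparing the difference in mean EHP-30 + 23 score and pain scores between groups with repeated measures (baseline, post-treatment, 3-months follow-up". It names no model term, contrast or visit, and no baseline covariate or constraint for the primary outcomes.

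Section {12} defines the primary outcomes as improvements in quality of life and pain, as well as "pain-related disability in the time between baseline and follow-up". It adds: "Greater improvements are expected in the intervention group compared to the control group". Both post-treatment and 3 months are listed as assessment times for both arms, and neither is ranked above the other.

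Baseline adjustment appears in {20a} only for secondary outcomes, where "we will use analysis of covariance models to conduct possibly necessary adjustment for baseline characteristics".

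The sample-size section {14} says "We estimated an effect size of *f* = 0.25" without stating which model term this effect size belongs to.

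**The concern.** Randomisation makes the expected arm difference at baseline zero. An analysis that treats baseline as one more outcome level must therefore say how it uses that level, and {20a} leaves two candidates open:

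- **Group main effect**, the more literal reading. The arm difference is averaged over all three occasions, so a known zero is averaged in.
- **Group-by-time interaction**, the reading that {12} favours. Change from baseline is compared between arms, but over two later visits at once. The test has 2 degrees of freedom, responds to any pattern of difference and is tied to no single pre-named estimate.

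Neither reading exploits the expected equality of the arms at baseline, although the baseline scores are collected anyway. The stake is power and a clear effect estimate for the primary claim. The two tests can also disagree on the same data, so naming neither leaves a choice open in a trial whose researchers are not blinded ({17a}).

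**Working it through.** **Inputs from the protocol.** N = 120 and f = 0.25 ({14}); 1:1 allocation ({8}), so 60 per arm; two-sided alpha .05 ({20a}); three visits ({20a}).

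**Assumptions.** The protocol gives no SD, correlation or effect pattern. I take SD 1 at each visit, compound symmetry with correlation r = .5 (range .3 to .7) and full data. The arm difference is 0 at baseline and 0.5 SD at both later visits; d = 0.5 is the two-arm equivalent of f = 0.25.

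**The plan's own figure.** A single two-arm comparison has noncentrality f²N = 0.0625 × 120 = 7.5, which gives 77.5% power; 95% would need N = 210. For the group effect over three visits, the noncentrality is 3f²N/(1+2r). At r = .5 this is 11.25, giving 91.4% power, and 95% would need N = 142. The usual interaction formula, 3f²N/(1−r), needs only 44 at r = .5. The group-effect formula gives 120 only at r of about .34 to .35. The stated N therefore does not show which test was meant.

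**Noncentrality.** With 60 per arm, a contrast with true difference δ and variance v has λ = 30δ²/v.

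1. Group main effect: δ = (0 + 0.5 + 0.5)/3 = 0.333 and v = (1+2r)/3. At r = .5, λ = 30 × 0.1111/0.6667 = 5.0.
2. Omnibus group-by-time test: the changes from baseline differ by (0.5, 0.5). Their covariance matrix is (1−r) times a matrix with 2 on and 1 off the diagonal. So λ = 30 × 2 × 0.25/[3(1−r)] = 5/(1−r). At r = .5, λ = 10.0 on 2 df.
3. Baseline-adjusted difference at 3 months: δ = 0.5 and v = 1−r². At r = .5, λ = 7.5/0.75 = 10.0 on 1 df.
4. Baseline-adjusted mean of both later visits: δ = 0.5 and v = (1+r)/2 − r². At r = .5, λ = 7.5/0.5 = 15.0 on 1 df.

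| Test | r = .3 | r = .5 | r = .7 |
|---|---|---|---|
| Group main effect | 70% | 60% | 53% |
| Omnibus, 2 df | 66% | 81% | 96% |
| Adjusted, 3 months only | 81% | 88% | 97% |
| Adjusted mean of both visits | 95% | 97% | 99.5% |

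At the first Holm step (alpha .025, r = .5) the four rows become 49%, 72%, 81% and 94%.

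**Other effect patterns, r = .5, alpha .05.**

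- Effect fades from 0.5 to 0.25 SD at 3 months. Omnibus: λ = 30 × 2 × (0.25 − 0.125 + 0.0625)/1.5 = 7.5, power 68%. Adjusted mean: λ = 30 × 0.375²/0.5 = 8.44, power 82%. Adjusted, 3 months only: λ = 30 × 0.0625/0.75 = 2.5, power 35%. Adjusted, post-treatment only: λ = 10.0, power 88%.
- Effect wholly absent at 3 months. Adjusted mean: λ = 30 × 0.25²/0.5 = 3.75, power 48%. Omnibus: λ = 30 × 2 × 0.25/1.5 = 10.0, power 81%.

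**The case against.** The strongest reply is that {12} speaks of greater improvement in one arm, which is a difference in change. Listing baseline as a repeated occasion is what a group-by-time test needs. On that reading baseline is taken into account through change, the comparison is a valid randomised one, and it does test differential improvement. This stands. A reader might infer that the plan tests something other than its primary outcome, or that the effect will certainly be diluted to 0.33 SD with 60% power. Those claims hold only under the main-effect reading, which {20a} permits but {12} does not favour.

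It can also be said that visit-specific estimates can be drawn from such a model, and that contrasts are often left to an analysis plan. The first is true, but none is pre-named. The second covers omitted detail. It does not cover what {20a} does state: baseline among the compared outcome levels, and adjustment for secondary outcomes only.

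A further objection is that fixing on 3 months alone is no clear gain. This also stands. Against the omnibus test its advantage nearly vanishes at r = .7 (96.7% against 96.2%), and it is much the weaker test if the effect fades (35% against 68% at r = .5).

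Finally, a reader might infer from the wording on secondary outcomes that covariates will be picked after seeing imbalance. The wording allows this but does not say it.

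**Conclusion.** The point holds as a weakness in how the primary test is specified and in its efficiency. It shows neither bias nor an inflated type I error.

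Under the favoured group-by-time reading and a sustained effect, the omnibus test gives up about 16 percentage points of power at r = .5 (81% against 97%). The loss is about 29 points at r = .3 and about 3 at r = .7. Under the main-effect reading the loss is larger: 37 points at r = .5, with the estimate cut by one third.

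These sizes rest on an assumed 0.5 SD effect at both later visits, compound symmetry and full data. The advantage of the adjusted mean persists for an effect that halves by 3 months, but reverses if the effect disappears by then. The failure to reproduce 120 reflects the unstated test and correlation; it does not prove that 120 is wrong.

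**What to change.** State in {20a} that the primary test for each primary score is one pre-set, baseline-adjusted between-arm contrast, with its 95% CI: the mean of post-treatment and 3 months. Estimate it from the repeated-measures model, with baseline means constrained equal across arms or with the baseline score as a covariate. Report the differences at each visit as supportive, and say in {12} that this contrast is the primary comparison.

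For secondary outcomes, replace the conditional wording with unconditional adjustment of each outcome for its own baseline value.

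This takes a few sentences and no new data, because baseline scores are already collected. The price is that the averaged contrast is weaker than a test at the right single visit when the effect is concentrated there (82% against 88% in the fading pattern). It is also weaker than the omnibus test if the effect exists at one visit only (48% against 81%). If the sponsor expects such a pattern, another pre-set, baseline-adjusted contrast can be named, but it must be fixed before the data are seen.

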### Methods in analysis to handle protocol non-adherence and any statistical methods to handle missing data {20c}

Data will be analyzed following the ITT principle. Missing data will be explored. Imputation of missing values is not intended, although multiple imputations might be used within sensitivity analyses assuming data are missing at random.

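### The primary model named in {20a}, a repeated-measures general linear model, does not in its ordinary form include everyone with at least one measurement, so model and inclusion rule contradict each other

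*Protocol article*

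**What the plan says.** Section {20a} of the protocol article makes three statements that bear on who is analysed.

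- The principle: "Analysis will be conducted based on the intention-to-treat (ITT) principle".
- The model: "Primary outcome analysis will be performed as a general linear model", comparing the arms on EHP-30+23 and pain scores, with baseline, post-treatment and 3-month follow-up as the repeated measures.
- The consequence drawn from that model: "With this approach, all participants providing data for at least one point of measurement will be included".

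Section {20c} adds the missing-data rule: "Imputation of missing values is not intended, although multiple imputations might be used within sensitivity analyses assuming data are missing at random". Section {20a} also promises sensitivity analyses on the influence of missing data, without saying which. Nowhere does the article name a mixed model, a likelihood-based method or generalised estimating equations.

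**The concern.** The inclusion sentence credits the named model with a property that its ordinary form lacks. A classical repeated-measures general linear model takes one outcome vector per participant and deletes anyone whose vector is incomplete. Since the main analysis does not impute, nothing in the plan brings those participants back.

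Two things are at stake. First, the analysed set: an analyst who follows the model's name gets complete cases, and one who follows the inclusion sentence must fit something else. According to {17a} the researchers are not blinded, so this choice should not be left until data are in hand. Second, bias: outcomes are collected by online self-report with no incentive to complete ({18a}, {18b}), and only the iCBT arm carries eight weekly modules of 1 to 2 hours each ({11a}). Drop-out that differs by arm is therefore plausible, though the document does not quantify it.

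**Working it through.** **1. The statements side by side.** (a) Repeated-measures general linear model on three assessments; (b) inclusion with at least one of the three; (c) no imputation in the main analysis. In the model's ordinary form, (a) with (c) means that all three values are required. That contradicts (b).

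**2. Demonstration.** One simulated data set had 120 participants and three visits, with 0%, 15% and 25% missing at baseline, post-treatment and follow-up (assumed). All 120 had at least one value and 82 had all three. The multivariate repeated-measures model used the 82. A likelihood-based linear mixed model used all 120 (320 observations).

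**3. The plan's own figure.** Section {14} gives 120 participants for f = 0.25, 5% significance and 95% power, without test family or correlation. Standard variants give 210 (one-way comparison), or 114 and 142 (between-group test on three measurements, correlation 0.3 and 0.5). So 120 is neither confirmed nor refuted. It serves here only as the number randomised.

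**4. Size of the loss.** No drop-out rate is given, so the share m missing at each later assessment is assumed. Baseline is taken as complete.

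| m | Independent: 120 × (1 − m)² | Monotone, m missing at last visit: 120 × (1 − m) |
|---|---|---|
| 10% | 97.2, i.e. 97 | 108 |
| 15% | 86.7, i.e. 87 | 102 |
| 20% | 76.8, i.e. 77 | 96 |

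**5. Power.** This uses the noncentral F distribution with f = 0.25, three measurements and correlation ρ = 0.5 (assumed). For the between-group test, λ = f² × N × 3 / (1 + 2ρ); at N = 120, λ = 0.0625 × 120 × 3 / 2 = 11.25 and power is 0.914. At 108, 96 and 84 complete cases it is 0.884, 0.844 and 0.792. For the group-by-time test, λ = f² × N × 3 / (1 − ρ); at N = 84, λ = 31.5 and power is still 0.999. The power loss therefore depends on which test is meant.

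**6. Bias, as an illustration.** Assumptions: true effect 0.50 SD at both later assessments; correlation 0.5 to 0.6; 15% random drop-out in controls; 23.5% in the iCBT arm, more likely with less improvement at post-treatment (logistic slope 0.5 to 1.5); 400,000 simulated participants per arm.

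| Analysis | Post-treatment | 3 months |
|---|---|---|
| Complete-case | 0.59 to 0.76 | 0.55 to 0.63 |
| Likelihood, post-treatment value of drop-outs observed | 0.50 | 0.50 |
| Likelihood, drop-out before the post-treatment assessment | 0.57 to 0.71 | 0.53 to 0.57 |

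In the second row the value driving drop-out is observed, so missing at random holds and the bias disappears. In the third row that value is itself missing, and the likelihood analysis removes only part of the bias.

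**The case against.** The strongest reply is that the inclusion sentence tells us what the authors meant. A general linear model with correlated errors, fitted by maximum likelihood or REML, accepts incomplete vectors and needs no imputation, which also fits {20c}. On that reading the model is misnamed and no complete-case analysis was chosen. The estimation method could also sit in a statistical analysis plan that is not shown. This much stands: a reader might infer that the trial has settled on a complete-case primary analysis, and the document does not support that. It follows only if the model's name overrides the explicit inclusion rule. What remains is that the article's own sentences conflict, and that the ordinary meaning of the name leads to listwise deletion.

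It is also fair that missing-data sensitivity analyses are planned. They lessen the risk but leave the primary estimate as it is, and multiple imputation is only a possibility there.

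Two further inferences go too far. One is that a mixed model would restore the true effect whatever the drop-out pattern; the third row of the bias table shows otherwise. The other is that including all 120 recovers the information of 120, since participants with a baseline value only add almost nothing to the treatment contrast. Finally, no fault is shown in the analysis of covariance for secondary outcomes.

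**Conclusion.** The contradiction is real and can be seen from {20a} and {20c} alone: the named model, in its ordinary form, cannot deliver the stated inclusion rule without imputation. Taken literally, the primary analysis would be complete-case under an intention-to-treat label.

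The size is conditional. With 10% to 20% missing at each later assessment, between 77 and 108 of 120 would be analysed, depending on whether missingness is independent or monotone. Power may fall noticeably or hardly at all. Under the assumed arm-specific drop-out, the complete-case effect is inflated in favour of iCBT. The drop-out rate and mechanism behind these figures are assumptions, because the document gives neither. The contradiction itself depends on none of them.

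**What to change.** In {20a}, replace the general linear model with a linear mixed model for repeated measures on baseline, post-treatment and 3 months. It would be fitted by REML, with fixed effects for visit, arm and arm-by-visit and a stated within-person covariance such as unstructured. State that it is valid under missing at random and that every randomised participant with at least one assessment enters it. The inclusion sentence can then stay as it is.

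If the classical model is preferred, the alternatives are to call the analysis complete-case or to move imputation into the primary analysis.

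In either case, specify at least one sensitivity analysis for data missing not at random. The multiple imputation mentioned in {20c} assumes missing at random, as the mixed model does, and so would not test that assumption.

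Constraining the baseline means to be equal, or using the same model for secondary outcomes, is optional and not needed to correct the error. The cost is one sentence in {20a} and a short addition to {20c}. Standard software suffices and no new data are needed.

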**Methods:**

This is a monocentric randomized-controlled trial recruiting 120 patients with endometriosis. The intervention consists of eight iCBT modules focusing on psychoeducation, cognitive restructuring, pacing, and emotion regulation. Participants will receive written feedback from a trained therapist weekly. The comparator is a waitlist control group. All participants will be followed up 3 months after the intervention, and the intervention group will additionally be followed up 12 months after the intervention. Trial participants will not be blinded to the allocated trial arm. Primary outcome measures are endometriosis-related QoL, pain, and pain-related disability. Secondary outcomes include coping, illness representations, and psychological flexibility. Statistical analyses will be performed following intention-to-treat principles.

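### The Holm correction counts two primary outcomes where the protocol nominates three (four scores if the pain measures are tested separately), so 5% family-wise control is not guaranteed

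*Protocol article*

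**What the plan says.** Three places in the protocol article bear on this.

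- **Abstract, Methods:** "Primary outcome measures are endometriosis-related QoL, pain, and pain-related disability". That is three outcomes.
- **Primary outcome measures, under Outcomes {12}:** "The primary outcomes are improvements in endometrioses-related QoL and pain during menstruation and across the cycle, as well as pain-related disability". These are the same three constructs, with pain given in two forms. Pain and disability have separate instruments: "Pain will be measured using visual analog scales", while disability has the seven-item PDI. For the EHP-30 + 23, "A score ranging from 0 to 100 is calculated for the core questionnaire as well as for each modular subscale"; no single total is described.
- **Statistical methods {20a}:** the primary model is described as "comparing the difference in mean EHP-30 + 23 score and pain scores between groups with repeated measures". Holm-Bonferroni is then brought in to "account for the testing of multiple hypotheses due to nomination of two primary outcomes". The general criterion is that "two-sided *p*-values < .05 will be considered statistically significant".

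The document does not rank the primary outcomes or define a composite pain score. The PDI does not appear among the secondary measures listed in {12}.

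**The concern.** Holm-Bonferroni protects the family-wise error only if its count equals the number of hypotheses tested. Here the stated count is smaller than the number of outcomes called primary, and one of those outcomes, the PDI, is not named in the sentence that describes the primary model. An analyst following the text could leave the PDI out, test it outside the family at .05, or run three or four tests against thresholds meant for two.

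At stake is the confirmatory efficacy claim. All outcomes are self-reported ({18a}), and neither researchers nor participants are blinded ({17a}). Quality of life is fixed by name as one of the two outcomes. What stays open is which score or scores on the pain and disability side make up the other, and that could be settled after results are known and still be defended from the text.

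**Working it through.** **Step 1. Count the outcomes under each reading.**

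- Pain scores exclude the PDI, and pain is one score: two tests, so the count of two fits, but the PDI has no confirmatory test.
- Pain scores exclude the PDI, and menstrual and cycle pain are tested separately: three tests, and the PDI is still left over.
- Pain scores include the PDI: at least three tests (QoL, pain, PDI), or four with two pain scales.
- Two means two domains, QoL and pain: the pain domain still holds several scores, with no rule for combining them. Holm counts hypotheses, not domains.

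No reading gives a count of two that covers every nominated primary outcome.

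**Step 2. Family-wise error.** Inputs from {20a}: two-sided 5% and a family of two, so the first Holm threshold is .05/2 = .025. When no outcome has a true effect, Holm makes a false claim exactly when the smallest p-value passes the first threshold. For independent tests:

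- two tests at .025: 1 − .975² = 4.94%
- three tests at .025: 1 − .975³ = 7.31%
- four tests at .025: 1 − .975⁴ = 9.63%
- Holm on two plus the PDI at .05: 1 − .975² × .95 = 9.69%
- Holm with a count of three (.05/3 = .0167): 1 − (1 − .05/3)³ = 4.92%
- Holm with a count of four (.05/4 = .0125): 1 − .9875⁴ = 4.91%

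The documents give no between-outcome correlation, so it is an assumption. The column for 0 is the closed form. The others come from 1,000,000 simulated sets of equally correlated two-sided z-tests under the global null.

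| Procedure | 0 | 0.3 | 0.5 | 0.7 | 0.9 |
|---|---|---|---|---|---|
| Holm for two, two tests | 4.94% | 4.80% | 4.68% | 4.30% | 3.61% |
| .025 on three tests | 7.31% | 6.99% | 6.58% | 5.73% | 4.35% |
| .025 on four tests | 9.63% | 9.04% | 8.29% | 6.94% | 4.93% |
| Holm for two, plus PDI at .05 | 9.69% | 9.26% | 8.72% | 7.63% | 6.05% |
| Holm for three | 4.92% | 4.72% | 4.49% | 3.90% | 2.98% |
| Holm for four | 4.91% | 4.66% | 4.34% | 3.65% | 2.60% |

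**Step 3. Power cost of a larger family.** Section {14} gives f = 0.25, p < .05, 95% power and N = 120, without the test or the within-person correlation, so 120 can be neither confirmed nor refuted. A between-group test on three measurements needs about 120 only if that correlation is about 0.33 to 0.36. Power at N = 120, with a within-person correlation of 0.5 assumed for the two repeated-measures tests:

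| Test | .05 | .025 | .0167 | .0125 |
|---|---|---|---|---|
| Between-group, three measurements | 91.4% | 85.9% | 82.1% | 79.2% |
| Group-by-time interaction | >99.9% | >99.9% | >99.9% | >99.9% |
| Two means at one time, d = 0.5 | 78.2% | 69.0% | 63.5% | 59.5% |

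**The case against.** The best defence is that {20a} names a valid method and states no thresholds. The .025 is inferred from the count of two. If the analyst runs Holm over every primary p-value actually produced, the error is held and only the stated count is wrong. The pain-scores term is plural and may be meant to include the PDI, which {12} describes in the same paragraph as the pain scales. The abstract speaks simply of pain, and {12} does not say that its two forms are tested separately.

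Much of this stands. Three primary outcomes are explicit; four tests are an inference. It cannot be said as fact that the PDI has no primary analysis, only that its place is unclear.

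A reader might also infer that the false-positive risk exceeds 5% however the text is followed. The documents do not support that. If pain is one score and the PDI is not tested as primary, the error is 4.94%. With correlations of about 0.9, the .025 threshold stays just under 5% on three or four tests.

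What does not stand is the idea that the count of two can be left alone. If the PDI is inside the pain scores, there are at least three hypotheses. If it is outside, a nominated primary has no stated test. Nor is this detail left to a fuller document: the count is stated and contradicted here, and {31c} says that no further protocol exists. A separate analysis plan would have to depart from either {12} or {20a}.

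**Conclusion.** The point holds as a contradiction between the primary outcomes listed in the abstract and {12} and the family size in {20a}. Its consequence is that control at 5% is not guaranteed, rather than a fixed inflation. At correlations from 0 to 0.7, the misapplied threshold gives about 5.7% to 7.3% for three tests and 6.9% to 9.6% for four; only near 0.9 does it fall below 5%. Testing the PDI outside the family at .05 exceeds 5% at every correlation examined, 9.7% down to 6.1%. These figures assume that no outcome has a true effect and that all pairs are equally correlated. The contradiction itself depends on neither assumption.

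**What to change.** Before data are analysed, make the abstract, {12} and {20a} agree. The sponsor can take either of two routes.

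1. **Keep all nominated primaries.** Name each primary score in all three places, including which EHP score is meant and which pain score or scores. Put the PDI explicitly in the sentence describing the primary model. Set the Holm family to that number: the first threshold is .0167 for three and .0125 for four.
2. **Keep two primaries.** Name exactly those two scores and move the others to secondary in all three places. Nothing in the document ranks the outcomes, so the choice is the sponsor's.

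The cost is rewording, plus either a stricter first threshold or fewer primary outcomes. Under the between-group test assumed above, power per outcome at the first threshold falls from about 86% at .025 to 82% at .0167 or 79% at .0125. The loss is negligible for the interaction test and larger for a single-time comparison of means. As {14} sizes the trial at p < .05, it should state the power at the threshold finally chosen.
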